#### Aim 2: Plan of analysis

Using Mplus, we will test the three hypotheses that coalitions receiving the Coalition Check-Up will implement EBPs with greater (1) quantity, (2) quality, and (3) sustainability as compared to the “TA as usual” condition. Prior to hypothesis tests, we will test for baseline differences on each of these dependent variables.

To test aim 2’s first hypothesis, we will model EBP quantity as a coalition-level dependent variable. Once we have three time points of data, we will estimate the developmental trajectory of EBP quantity with growth models—following aim 1 procedures to identify the best functional form of the growth model. Once the developmental trajectory of EBP quantity is properly modeled, it will be predicted by the experimental condition (0=control; 1= Coalition Check-Up) [62].

For the second hypothesis—i.e., programs implemented by coalitions in the Coalition Check-Up condition have superior implementation quality—the unit of analysis is program level, nested within coalition level. Thus, the analytic model will estimate a random intercept. As in the first hypothesis, growth modeling procedures will estimate the developmental trajectory of EBP quality. Experimental condition (0=control; 1= Coalition Check-Up) will be entered at the level of the coalition. Program type (i.e., school-based curriculum, therapist-driven, mentoring, parent curriculum) and program complexity will be covariates at the program level.

For the third hypothesis—i.e., programs implemented by Coalition Check-Up coalitions have superior sustainability—we will test overall EBP sustainability and sustainability planning separately. Coalition Check-Up impact on sustainability planning will be estimated with a multilevel model accounting for the nesting of programs within coalitions. Program-level covariates include program type, program complexity, and baseline EBP longevity. Since overall EBP sustainability is a coalition-level dependent variable, the regression model will not need to adjust for the nesting of programs within coalitions. As with prior models, experimental condition (0=Control; 1= Coalition Check-Up) will be entered at the coalition level.

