Mediation analyses will test whether coalition capacity mediates between intervention condition and EBP implementation. We will test whether coalition capacity has significant direct and indirect effects on each EBP implementation measure: (a) quantity, (b) quality, and (c) sustainability. Each of these outcomes will be modeled as previously described in this aim, with the addition of the coalition capacity mediational pathway [63, 64].

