Building from models of the Coalition Check-Up’s overall effects on youth substance use, we will test whether EBP implementation mediates between the experimental condition and youth substance use. We will test the EBP implementation measures described in Aim 2 (quantity, quality, sustainability) in separate mediation models. Each model will test for both direct and indirect effects on youth substance use—aggregate 30-day use, and aggregate lifetime use measures of alcohol, tobacco, marijuana, and opioids. If a mediational pathway is significant, we will conduct follow-up analyses modeling each of the specific substances separately [63, 64].

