## Discussion

This innovative trial tests a unique approach to supporting community coalitions’ implementation of EBPs. Other low-cost TA models are typically expert driven and specific to a single type of coalition [16]. In contrast, the Coalition Check-Up supports coalition-driven action planning. Unlike existing TA models, the Coalition Check-Up can also be applied broadly across coalition models because it focuses on common dimensions of coalition capacity and EBP implementation linked to youth outcomes [20, 21]. The proactive, data-driven monitoring in this study involves continuous quality improvement cycles that identify TA needs and provide timely support to improve capacity [69]. The Coalition Check-Up is unique in its use of motivational interviewing to support its audit and feedback implementation strategy, thereby strengthening the collaborative working relationship, enhancing coalition-driven action planning, and coalition commitment to making change [70, 71].

Using the Interactive Systems Framework and an extensive history of coalition research, this study will examine causal pathways from TA to EBP implementation and youth outcomes [22, 24, 26]. In this way, the study advances the field of implementation science by providing new evidence of the relationship between Interactive Systems Framework domains and implementation outcomes. The scale of this project allows for longitudinal testing of mediating pathways from Coalition Check-Up to distal community-wide outcomes. Together, these innovations will yield evidence about not only if but also how the Coalition Check-Up works. Advancement of the Coalition Check-Up evidence-base will encourage model usage as a low-cost and generalizable approach for supporting coalitions to achieve community-wide reductions in youth substance use.

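### The mediation models name no coalition-level confounder and no unconditional baseline for the mediator-to-outcome path, so confounding alone could pass as a causal pathway if the Check-Up moves capacity

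*Protocol article*

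**What the plan says.** All references are to the protocol article.

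- **Aim 2: Plan of analysis, mediation paragraph.** The test is stated as "We will test whether coalition capacity has significant direct and indirect effects on each EBP implementation measure", and the model is fixed by reference back: "Each of these outcomes will be modeled as previously described in this aim, with the addition of the coalition capacity mediational pathway".
- **Aim 2: Plan of analysis, outcome models.** For quantity: "Once the developmental trajectory of EBP quantity is properly modeled, it will be predicted by the experimental condition"; no other predictor is named. For quality, program type "and program complexity will be covariates at the program level". For sustainability planning: "Program-level covariates include program type, program complexity, and baseline EBP longevity". Overall sustainability is a coalition-level regression on condition. The quantity paragraph takes over from Aim 1 only the procedure for choosing the functional form.
- **Data analytic plan, Aim 1.** Control for potential confounders and inclusion of year-0 measures are stated here, where capacity is the outcome.
- **Aim 3: Analyses.** Baseline youth use becomes a covariate only if the arms differ on it. The mediation models then follow: "Each model will test for both direct and indirect effects on youth substance use".
- **Randomization.** TA availability, years in operation, coalition model, population density, poverty rate and funding availability are known for matching. None is named in the Aim 2 or Aim 3 models.
- **Discussion.** "this study will examine causal pathways from TA to EBP implementation and youth outcomes". The Abstract and the Contributions to the literature also speak of causal pathways.

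**The concern.** Randomization protects the path from condition to capacity. It does not protect the path from capacity to EBP implementation, or from EBP implementation to youth use. A coalition trait that raises both mediator and outcome makes that second path non-zero even when the mediator does nothing.

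The article itself points to such traits. Under Coalition recruitment, activity levels are said to move with funding. The Background reports that engagement and activities tend to decline when TA funding ends. Availability of funding is also part of the definition of a non-operational EBP. Overall sustainability counts years of operation for programs that already existed as well as new ones, so pre-trial program load passes straight into the outcome.

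Confounder control is stated for the randomized comparison (Aim 1) and not for the non-randomized path, where it is needed most. At stake is the claim to have tested the pathways of the Interactive Systems Framework. The Aim 1 to 3 comparisons of the arms are unaffected.

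**Working it through.** **Plan's own figures.** The Power analysis gives d = .24 to .37 (Aim 1), .31 to .42 (Aim 2) and .25 (Aim 3) at power .80. It gives no figure for the mediation tests, so there is nothing to reproduce for them.

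**Inputs.** From the article: 68 coalitions, one of each matched pair per arm, hence 34 v 34. Assumed: two-sided 5% tests; true capacity effect on EBP implementation = 0; within-arm capacity-EBP correlation r from shared causes, shown from 0 to .49. Mediation is declared when the condition-to-capacity path (a) and the capacity-to-EBP path (b) are both significant. This simplifies the multilevel models to coalition level.

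**Step 1, path a.** For a coalition-level measure without covariates, power ≈ Φ(d·√(34/2) − 1.96).
- d = .37 (top of the Aim 1 range): .37 × 4.123 = 1.526; Φ(−0.434) = .33.
- d = .69: 2.845; Φ(0.885) = .81, taken as .80, the power the plan states.

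**Step 2, path b.** Rejection probability ≈ Φ(z − 1.96) + Φ(−z − 1.96), with z = atanh(r)·√(68 − 4) = 8·atanh(r).

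**Step 3, product of the two.**

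| r | z | path b rejects | false mediation, d = .37 | false mediation, d = .69 |
|---|---|---|---|---|
| 0 | 0 | .05 | 2% | 4% |
| .25 | 2.04 | .53 | 18% | 43% |
| .36 | 3.02 | .85 | 28% | 68% |
| .49 | 4.29 | .99 | 33% | 79% |

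Simulation of the same unadjusted single-wave model agrees: about 17% / 29% / 33% at d = .37 and 43% / 68% / 80% at d = .69, for r = .25 / .36 / .49. If the Check-Up does not move capacity, path a rejects 5% of the time and the rate cannot exceed about 5% at any r.

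**Step 4, other model forms (simulated, d = .69, r = .3 / .5).** The stable trait is given an assumed year-to-year stability of .7.

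| Model | Stable confounder | Time-varying confounder |
|---|---|---|
| No adjustment | 57% / 80% | 56% / 81% |
| Year-0 capacity and year-0 outcome adjusted | 7.5% / 17% | 67% / 83% |
| Change-on-change (slope form) | 5% / 5% | 32% / 50% |
| Confounder itself adjusted | 5% / 5% | 4% / 4% |

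The gain from year-0 adjustment depends on the stability assumed. If stability is no higher than r itself, the adjusted rates at r = .25 / .36 / .49 are about 22% / 34% / 49%; with stability .7 they are about 5% / 11% / 16%.

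**The case against.** The strongest reply is that Step 3 is not the planned model for every outcome. Quantity and quality are growth models on annual data, and so is capacity. Stable differences between coalitions go into intercepts, so relating slope to slope brings the error back to about 5%. This stands for a stable confounder. But the mediation paragraph does not say that mediation runs slope on slope, and that form does not remove time-varying confounding, which is how the article describes funding. Nor does it reach overall sustainability, a single sum over years 2-4, or the Aim 3 models, which are fitted to year-3 and year-5 outcomes. Sustainability planning lies between: its model adjusts for baseline EBP longevity at program level.

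A second reply is that covariates and sensitivity analyses belong in the full protocol or SAP, and that the mediation method is referred to cited sources. Neither is shown, and silence alone would be no finding. Here, however, the article defines the mediation model by pointing to outcome models whose predictors it lists, and then draws a causal conclusion.

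A reader might infer that the trial will usually declare mediation falsely. The documents do not support that. It needs both a real effect on capacity and a shared-cause correlation of about .2 or more, and the documents establish neither. A reader might also infer that baseline adjustment can only halve the error; that rests on tying year-to-year stability to the confounding correlation.

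**Conclusion.** The point holds in conditional form. As written, the non-randomized path in the mediation models has no coalition-level confounder and no unconditional baseline of mediator or outcome, while the result is called causal. If the Check-Up moves capacity and r is about .25 to .5, an unadjusted model not in slope form declares mediation without any capacity effect in about 17-35% of trials at d = .37 and about 40-80% at d = .69, against at most about 5% without confounding. Both r and the true effect on capacity are assumptions.

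The reach is fullest for overall EBP sustainability. The same gap exists in the Aim 3 mediation models, although the percentages were worked for capacity and EBP implementation only. For quantity and quality it depends on a model form the article leaves open. This should be changed; it does not threaten the main comparisons.

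**What to change.** 1. In every Aim 2 mediation model, adjust both the mediator and the outcome equation for year-0 capacity, the year-0 EBP measure (for overall sustainability, baseline EBP count or longevity) and the main matching factors, at least funding and TA availability.
2. In the Aim 3 mediation models, adjust for year-0 EBP implementation and baseline community youth use whether or not the arms differ.
3. State whether mediation for quantity and quality relates slope to slope.
4. Because baseline adjustment is only partial, report for each indirect effect the residual mediator-outcome correlation at which it becomes zero. Describe results that are not robust to a correlation stated in advance as associations.

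The cost is wording and modest extra analysis: matching factors and annual measures are already collected. The downside is a few degrees of freedom with 68 coalitions, which is why only the main matching factors are required, and more cautious mediation claims.

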#### Aim 3: Analyses

The final aim will be to test the hypothesis that communities receiving the Coalition Check-Up will reduce youth substance use relative to communities in the “TA-as-usual” condition. Youth reports of substance use will be nested in school district (i.e., community or coalition level) via multilevel models. We will start by testing for differences in baseline levels of youth substance use between the two experimental conditions, to examine balance after randomization. If these comparisons identify a difference between the two conditions on a particular measure, it will be included as a covariate in the modeling. Then, youth substance use outcomes in year 3 will be predicted by experimental condition. A longer-term analysis of the Coalition Check-Up’s impact on youth substance use becomes possible with year 5 outcome data. These longer term outcomes will capture the effect of the Coalition Check-Up delivered as a continuous quality improvement cycle over years 2–4 of the study. We will use the same analytic models in year 5 as year 3, given that the data is identifiable at the school-district level but not the student-level.

We will examine 8 youth substance use outcomes (see the “Aim 3: Measures—youth substance use” section) in two multivariate multi-level models [62]. The first model will test past 30-day use of alcohol, tobacco, marijuana, and opioids simultaneously within the coalition’s catchment area [62]. The second model will test lifetime usage outcomes of the same substances. If an overall significant effect is found for the Coalition Check-Up in a particular multivariate model, follow-up tests will examine the specific substances as separate dependent variables [62]. These models extend analyses of Pennsylvania Youth Survey data conducted by [name] and [name] by taking advantage of increased levels of survey participation, the availability of community-level pretest measures of youth substance use, and the collection of detailed EBP implementation data [24, 59, 65].

Building from models of the Coalition Check-Up’s overall effects on youth substance use, we will test whether EBP implementation mediates between the experimental condition and youth substance use. We will test the EBP implementation measures described in Aim 2 (quantity, quality, sustainability) in separate mediation models. Each model will test for both direct and indirect effects on youth substance use—aggregate 30-day use, and aggregate lifetime use measures of alcohol, tobacco, marijuana, and opioids. If a mediational pathway is significant, we will conduct follow-up analyses modeling each of the specific substances separately [63, 64].

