### Coalition recruitment

We will recruit 68 coalitions from community anti-drug coalitions across Pennsylvania and Missouri, USA. This coalition population is similar to other US coalitions, which enhances study generalizability. These coalitions have received funding from a wide variety of sources, and their activity levels have fluctuated with changes in funding levels over time. Coalitions function in rural, suburban, and urban areas, ranging in age from 1 to 30 years old. We connect with these coalitions through the Evidence-based Prevention and Intervention Support (EPIS) group in the Pennsylvania State University’s Prevention Research Center. The EPIS team interfaces with community agencies, schools, and coalitions to provide support to those attempting to integrate prevention research into their practices.

We are using a layered targeted strategy to recruit coalitions, first with email communications from EPIS TA staff. We then introduce the project at coalition regional meetings organized by EPIS, providing time for questions and small group discussion to connect project researchers with coalition members. We then conduct follow-up phone calls and online meetings. The decision to participate rests on each coalition’s leadership team or at times with the full coalition.

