### Randomization

Matched pairs of coalitions will be randomly assigned to the Coalition Check-Up condition or TA as usual. Coalitions will be matched on level of TA availability at baseline (0 = none, 1 = occasional trainings and group TA, 2 = regularly scheduled group TA, 3 = group TA and regularly scheduled one-on-one supervision, 4 = regularly scheduled one-on-one capacity-building TA), years in operation, coalition model employed, population density, US Census poverty rate, and availability of funding. A random number seed will be generated by an external third party using random.org. SAS Proc Surveyselect uses this random number seed to select one of each pair of coalitions recruited into the study as the intervention condition. Data collectors and data analysts will be blind to study condition, with no circumstances under which unblinding is permissible.

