#### Aim 3: Data collection—youth substance use

We will measure youth substance use and related behaviors with the Pennsylvania Youth Survey and the Missouri Student Survey—statewide surveys similar to the Communities That Care Youth Survey [52]. In 2019, 413 out of 500 (83%) school districts in Pennsylvania participated, and in 2018, 102 of 115 (89%) counties participated in Missouri [53, 54]. The surveys are conducted free of charge in all schools in Pennsylvania and Missouri by their state governments. Survey data are collected every other year in 6th, 8th, 10th, and 12th grades. All instruments are available from the first author.

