#### Aim 3: Measures—youth substance use

We use measures from the Pennsylvania Youth Survey and Missouri Youth Survey which include items measuring substance use, along with several risk and protective factors [24, 58]. There are 8 key variables under investigation in this study: dichotomized lifetime use and 30-day use of alcohol, tobacco, marijuana, and opioids, respectively [58, 59].

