### Power analysis

We used Optimal Design to estimate power for cluster-randomized trials [60]. In this study, youth-level substance use data and program-level implementation data are clustered within coalitions, which is the level of random assignment. Overall, we will have a power of .80 to detect Cohen’s *d* effect size ranges as follows: aim 1, .24 to .37, a small to medium effect, depending on the measure of coalition capacity; aim 2, .31 to .42, a medium effect, depending on the EBP implementation measure; and aim 3, .25, a small effect, for measures of youth substance use.

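### The lifetime-use model is diluted by use that began before delivery, chiefly in older grades and at year 3, and baseline use is adjusted for only conditionally

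*Protocol article*

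**What the plan says.** Aim 3: Measures lists eight key youth outcomes: "dichotomized lifetime use and 30-day use of alcohol, tobacco, marijuana, and opioids, respectively". Aim 3: Analyses puts the four 30-day outcomes in one multivariate multilevel model and the four lifetime outcomes in another: "The second model will test lifetime usage outcomes of the same substances". A significant overall result in either model opens the substance-specific tests within that model.

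On the population, Aim 3: Data collection says: "Survey data are collected every other year in 6th, 8th, 10th, and 12th grades". The analysis section states no grade restriction or grade term for the lifetime model.

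On timing, outcomes are analysed in year 3 and again, with the same models, in year 5. The Check-Up is "delivered as a continuous quality improvement cycle over years 2–4 of the study". Intervention procedures cites earlier coalition research that an effect on youth use takes two to three years to appear.

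On baseline, Aim 3: Analyses makes a youth-use measure a covariate only if the arms are found to differ on it at baseline. The data identify the school district but not the student. The mediation analyses use aggregate lifetime use as one of their two outcomes.

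Power analysis gives one figure for all of this: "aim 3, .25, a small effect, for measures of youth substance use".

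**The concern.** Ever-use cannot be undone. A student who first used before year 2 is a lifetime user at year 3 and year 5 whatever the coalition does. The share of such students should be largest in grades 10 and 12, where most of the time at risk lies before delivery, and at year 3, when delivery has run for about one year and at most two. That is at or before the lower end of the lag the protocol itself expects.

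Earlier use also varies between districts. The matching factors in the Randomization section do not include youth substance use, and the covariate rule adjusts for it only when a difference shows up. Unless that happens, variation that the intervention could not have changed stays in the error term.

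At stake is the sensitivity of four of the eight key youth outcomes and of the lifetime mediation models. A null year 3 lifetime result could be taken as evidence against prevention when the window was too short for much to change.

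**Working it through.** **The protocol's own figure.** Inputs from the protocol are 68 coalitions ("We will recruit 68 coalitions from community anti-drug coalitions across Pennsylvania and Missouri, USA"), one of each pair to intervention ("select one of each pair of coalitions recruited into the study as the intervention condition"), and power .80. The intraclass correlation ρ, the students per cluster n and alpha are not given; I assume two-sided alpha of 0.05. For a two-level cluster trial with 66 degrees of freedom:

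MDES = (t.975 + t.80) × √(4 × (ρ + (1−ρ)/n) / 68), with t.975 + t.80 = 2.844.

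Setting MDES = 0.25 gives ρ + (1−ρ)/n = (0.25/2.844)² × 68/4 = 0.131, for example ρ = 0.13 with n = 500. With ρ from 0.01 to 0.10 and n from 100 to 1000, the MDES is 0.07 to 0.23. So d = .25 can be neither confirmed nor refuted. It is a detectable effect, not a required one.

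**Dilution, all grades pooled.** The protocol gives no onset data, so I assume four patterns of yearly onset hazard, equal grade weights, onset counted from grade 3.0 and survey at grade + 0.5:

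- A: 0.10 from grade 4 on.
- B: 0.02 before grade 6, 0.06 in grades 6–8, 0.15 in 8–10, 0.25 after.
- C: 0.05, 0.15, 0.20, 0.20 over the same bands.
- D: 0.003, 0.015, 0.03, 0.05 over the same bands.

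Ever-use is 1 − exp(−cumulative hazard). Cutting the hazard by a fraction r during delivery lowers ever-use, and d = (difference in log-odds) × √3/π.

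Worked case, pattern A with one year of delivery: ever-use in grades 6, 8, 10 and 12 is 22.1, 36.2, 47.8 and 57.3%, mean 40.85%. Ever-use before delivery is 13.9, 29.5, 42.3 and 52.8%, mean 34.63%. The pre-delivery share is 34.63/40.85 = 85%. If all new onset stopped, the log-odds would move from −0.370 to −0.635, so d = 0.265 × 0.5513 = 0.15.

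Ranges over the four patterns:

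| Delivery before survey | Grade 12 users pre-dating | Grade 10 | Pooled | Pooled d, onset cut 25% | cut 50% | stopped |
|---|---|---|---|---|---|---|
| 1 year | 80–92% | 69–89% | 72–85% | 0.03–0.05 | 0.07–0.10 | 0.15–0.22 |
| 2 years | 58–83% | 45–76% | 49–68% | 0.07–0.09 | 0.15–0.19 | 0.32–0.45 |
| 3 years | 40–74% | 27–62% | 31–52% | 0.10–0.12 | 0.22–0.26 | 0.51–0.71 |

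With three years, the pre-delivery share is 14–38% in grade 8 and 0–12% in grade 6. The effect is assumed to begin on the first day of delivery; a lag would make the dilution worse.

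**Which earlier cohort is available.** The surveys are biennial and cover even grades, so the same school cohort recurs. If the last pre-delivery survey falls two years before the year 3 survey:

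| Grade at outcome | Year 3: earlier grade | Year 5: earlier grade |
|---|---|---|
| 6 | 4, not surveyed | 2, not surveyed |
| 8 | 6 | 4, not surveyed |
| 10 | 8 | 6 |
| 12 | 10 | 8 |

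The match exists for grades 10 and 12 at both times, which is where the dilution is largest.

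**Why conditioning helps.** A district-level covariate that explains a share R² of the between-district variance replaces ρ by ρ(1−R²) in the formula. At ρ = 0.13 and n = 500 the between-district part is 0.13 of 0.1317 (0.87/500 = 0.0017 is the rest), so the MDES shrinks almost in proportion to √(1−R²). The documents give no R², so I put no figure on the gain.

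**The case against.** The strongest reply is that nothing here biases the trial. Earlier users are balanced by randomisation in expectation. The 30-day outcomes, listed first, have their own model and do not share the problem. A null lifetime model stops only the lifetime follow-up tests. The handling of grade may also sit in a fuller protocol or analysis plan that is not shown. All of this stands. What it does not answer is the covariate rule: that is a stated choice, and it leaves earlier use unadjusted unless a difference appears.

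Three stronger readings are tempting, and the document supports none of them.

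- A reader might infer that the lifetime model cannot show an effect. Under the assumptions above, only at year 3 with about one year of delivery would even a complete stop of new onset fall short of d = .25. By year 5, halving onset reaches about that size. With a smaller ρ than the stated d = .25 seems to imply, smaller effects would be detectable.
- A reader might infer that most older lifetime users started before delivery. That holds under all four patterns for grades 10 and 12 after one year and for grade 12 after two, but not under every pattern for grade 10 after two years or for either grade after three.
- A reader might conclude that the lifetime model should be confined to grades 6 and 8. That drops about half the students and keeps the grades with the lowest prevalence, a particular problem for opioids. It is a debatable trade-off, not a correction.

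**Conclusion.** The point holds as a loss of sensitivity. The lifetime model, with no stated grade restriction, is diluted by use that began before year 2, most in grades 10 and 12 and at year 3. The conditional baseline rule leaves between-district variation in that earlier use as noise, in both the lifetime model and the lifetime mediation models. The comparison stays unbiased and is not uninformative, and Aim 3 does not rest on it alone.

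The size is conditional on my assumed hazards, equal grade weights and an immediate effect. With one year of delivery, a halving of new onset shows as a pooled d of about 0.07–0.10; with three years, about 0.22–0.26. The single d = .25 shows no separate allowance for this, but without ρ and n it cannot be called wrong.

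**What to change.** Keep all four grades in the lifetime model, and change the following.

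1. Always, not only when a baseline difference is found, condition lifetime use in grade g on the same district's pre-delivery lifetime prevalence in the same school cohort: grade g−2 for the year 3 survey and g−4 for year 5. Where that cohort was too young to be surveyed, use the district's same-grade pre-delivery prevalence. Do the same in the lifetime mediation models. Set the lag by state from the last survey before delivery: the protocol reports participation for 2019 in Pennsylvania and 2018 in Missouri, which suggests that the two biennial cycles fall in alternate years.
2. Include grade and a grade-by-condition term.
3. Name year 5 as the main time point for lifetime use, and say in advance that a null year 3 lifetime result is limited by short exposure.
4. If a grades 6 and 8 analysis is wanted, report it as a sensitivity analysis.

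This is a change of analysis wording and needs no new data collection. The cost is a few extra district-level covariates among 68 clusters and dependence on each district having taken part in the pre-delivery survey.
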